**Methods:**

Sixty-two individuals with chronic hemiparesis will be randomized into two groups: Aerobic exercise + m-CIMT or Stretching + m-CIMT. m-CIMT includes 1) restraint of the nonparetic upper limb for 90% of waking hours, 2) intensive task-oriented training of the paretic upper limb for 3 h/day for 10 days and 3) behavior interventions for improving treatment adherence. Aerobic exercise will be conducted on a stationary bicycle at intervals of moderate to high intensity. Participants will be evaluated at baseline, 3, 30, and 90 days postintervention by the following instruments: Motor Activity Log, Nottingham Sensory Assessment, Wolf Motor Function Test, Box and Block Test, Nine-Hole Peg Test, Stroke Specific Quality of Life Scale and three-dimensional kinematics. The data will be tested for normality and homogeneity. Parametric data will be analyzed by two-way ANOVA with repeated measures and Bonferroni’s adjustment. For nonparametric data, the Friedman test followed by the Wilcoxon test with Bonferroni’s adjustment will be used to compare the ratings for each group. To compare the groups in each assessment, the Mann-Whitney test will be used.

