### Sample size

The sample size was calculated with G*Power software using the independent t-test, 85% power, alpha 0.05, and 20% drop-out. Data from the Nine-Hole Peg test proposed by Yoon et al. (2014) [29] were considered for this calculation. Thus, a sample size of 78 individuals (39 per group) is required for this study (Fig. 1). However, after collecting the first five participants per group, the sample size will be recalculated for the same variable.

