### Statistical analysis

Demographic characteristics, such as weight, height and body mass index, will be presented as the mean and standard deviation. Median, maximum and minimum values will be used to describe poststroke time and UE-FMA score.

For all dependent variables, normality (Kolmogorov-Smirnov) and homogeneity (Levene) tests will be applied. If the variables present a normal and homogeneous distribution, then two-way analysis of variance with repeated measurements and Bonferroni’s correction will be used to examine the effect of group-by-evaluation time interaction, group (AE + m-CIMT and Stretching + m-CIMT), and evaluation time (baseline, 3, 30 and 90 days after the intervention). To protect against Type I error, Bonferroni’s correction will be used. Thus, each of the 10 planned comparisons will have to achieve *p* = 0.005 for statistical significance. The partial eta squared (η^2^) will be used to determine the effect size of the intervention. The mean difference from pre- and post-interventions and the corresponding 95% confidence interval (95% CI) will be calculated for each group (EA + m-CIMT and Stretching + m-CIMT) in order to estimate the effect of the intervention.

Otherwise, the Friedman test (*p* < 0.05) will be used followed by the Wilcoxon test with Bonferroni’s adjustment (*p* < 0.008) to compare evaluation time for each group baseline, 3 days, 30 days, 90 days after the end of treatment. The Mann-Whitney test with Bonferroni’s adjustment (*p* < 0.012) will be used to compare the groups in each time evaluation (EA + m-CIMT and Stretching + m-CIMT).

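### The 85% power is calculated at alpha 0.05, but a single between-group comparison is judged at 0.012, or probably 0.005, where power is about 65–68% or 56%

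*Protocol article*

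**What the plan says.** The Sample size section describes a calculation "using the independent t-test, 85% power, alpha 0.05, and 20% drop-out", based on NHPT data from a cited study. It concludes that "a sample size of 78 individuals (39 per group) is required for this study" and adds that the number will be recalculated for the same variable after the first five participants per group. It mentions no multiplicity adjustment, either in the calculation or in the planned recalculation.

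The Statistical analysis section sets other thresholds. If the data are normal and homogeneous, a two-way repeated-measures ANOVA is used with Bonferroni's correction. The rule is then: "Thus, each of the 10 planned comparisons will have to achieve" p = 0.005. The ten comparisons are not listed, and no alpha is given for the ANOVA's own interaction, group and time tests. Otherwise the Friedman test is used at 0.05, followed by Wilcoxon tests at 0.008 between visits, and "The Mann-Whitney test with Bonferroni’s adjustment (*p* < 0.012) will be used to compare the groups in each time evaluation".

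**The concern.** Power is a property of a test together with its significance threshold. The trial is sized on a two-group comparison at 0.05, yet where the document attaches a threshold to a two-group comparison it is 0.012, and on the parametric route probably 0.005. A reader of the sample size section would believe that a true effect of the planned size has an 85% chance of being declared. For the contrast that was sized, under the thresholds that were written, that is not so. A null result on that contrast could then be read as evidence against aerobic priming from a trial reported as 85% powered.

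The trial's hypothesis is between groups: aerobic exercise adds to the effect of m-CIMT on dexterity. If the family of ten is what it appears to be, this contrast shares its alpha with changes over time within the sample and with a baseline comparison of randomised groups. Neither of those tests the hypothesis.

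**Working it through.** **Inputs from the protocol.** Independent t-test, 85% power, alpha 0.05, 20% drop-out, 39 per group (Sample size). Thresholds 0.005, 0.008 and 0.012 (Statistical analysis).

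**Assumptions.** The design test is two-sided (not stated). The effect size and SD are not given, so the effect is back-solved.

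**Reproducing the plan's own figure.** The base number cannot be reproduced without the effect size. The drop-out step can: 31 / (1 − 0.20) = 38.75, rounded up to 39 per group, 78 in total. The abstract's 62 equals 2 × 31, and 62 / 0.8 = 77.5, rounded up to 78. So 31 evaluable per group is the natural reading.

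**Where the thresholds come from.** 0.05 / 6 = 0.0083 for the six pairs among four visits; 0.05 / 4 = 0.0125 for group comparisons at four visits; 0.05 / 10 = 0.005. Since 6 + 4 = 10, the group contrasts are probably among the ten. This is an inference from the count.

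**Implied effect.** For n per group, t has 2n − 2 degrees of freedom and noncentrality d√(n/2). With n = 31, setting power to 85% at two-sided 0.05 gives d = 0.774 (noncentrality 3.045, critical value 2.000).

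**Power at the written thresholds, same d and n**

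| Two-sided alpha | Critical t (60 df) | Power, 31 per group | Power, 39 per group (no drop-out) |
|---|---|---|---|
| 0.05 | 2.000 | 85.0% | 92.1% |
| 0.012 | 2.591 | 67.5% | 79.7% |
| 0.005 | 2.915 | 55.5% | 69.9% |

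The critical values shown are for 31 per group. The 0.012 threshold belongs to a Mann-Whitney test. With its asymptotic efficiency of 0.955 relative to the t-test under normality, power at 31 per group is about 65%, hence the range 65–68%.

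**Sensitivity to the undisclosed effect.** If the calculation had instead treated 39 per group as evaluable, then d = 0.687 and power is 55.9% at 0.005 and 67.7% at 0.012. The normal approximation Φ(1.960 + 1.036 − z), which needs neither d nor n, gives 57.5% at 0.005 (z = 2.807) and 68.6% at 0.012 (z = 2.512). The loss comes from the change of alpha, not from the assumed effect. If the design alpha was one-sided, the loss is larger: about 52% at one-sided 0.005 with 31 per group.

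**Size needed to keep 85% with d = 0.774 (t-test).** At 0.005: 52 evaluable per group, 52 / 0.8 = 65 enrolled per group, 130 in total. At 0.012: 44 evaluable, 44 / 0.8 = 55 enrolled per group, 110 in total.

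**The case against.** The strongest reply is that 0.005 may not be the threshold that decides the trial. The section names the omnibus tests first and attaches 0.005 only to the planned comparisons. The Friedman test on the other route is explicitly at 0.05, with Bonferroni thresholds for the follow-up tests. An interaction tested at 0.05, with 0.005 reserved for follow-up contrasts, is therefore an open reading. This stands: the 56% is not the power of such an interaction test. It does not remove the point, because the sizing test was a two-group t-test rather than an interaction, and the 0.012 threshold is explicitly for comparing groups. A repeated-measures analysis may be more efficient than the t-test, but the document claims no such gain and gives no correlation.

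A reader might also infer that a true effect would be missed almost half the time. The documents do not support that for the trial as a whole. It is the miss rate for one contrast at 0.005, whereas groups are compared at several visits and no single visit is named as primary. If the effect persisted unchanged at all three post-treatment visits, simulation with 31 per group gives the following chance of at least one significant t-test for between-visit correlations of 0.5 to 0.9: about 80% down to 67% at 0.005, and about 89% down to 77% at 0.012. Persistence and the correlations are assumptions, and at 0.005 the chance still stays below 85%.

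Finally, the sample size is provisional, since it will be recalculated. That does not repair the mismatch, because the recalculation is not tied to an adjusted alpha either.

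**Conclusion.** The stated 85% does not describe the stated thresholds. For a single between-group contrast with the design's implied effect, power is about 65–68% at 0.012. It is about 56% at 0.005 if the group contrasts are among the ten comparisons. With no drop-out the t-test figures are about 80% and 70%, still short of 85%. The results assume a two-sided design alpha and a back-solved effect, but they hardly depend on the size of that effect.

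This is an inconsistency between design and analysis, not a slip in arithmetic: the Bonferroni division and the drop-out inflation are both correct. Nor does it follow that the NHPT at 3 days must become the only confirmatory test. The protocol lists the Motor Activity Log and the Box and Block Test alongside the NHPT as primary measures, and it names no primary visit. Choosing one is a design decision for the sponsor.

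**What to change.** Reconcile the two sections in one of two ways.

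1. **Keep the thresholds and restate the power.** Say which comparisons make up the ten and which test and alpha decide the between-group question. Give the power in the Sample size section at that threshold (about 56% at 0.005, about 65–68% at 0.012), and use the same alpha in the planned recalculation. The cost is a less favourable stated power or, if 85% is to be kept on the t-test basis, enrolment of about 130 (at 0.005) or 110 (at 0.012) instead of 78.

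2. **Keep the sizing and match the test to it.** State that the between-group NHPT contrast, at one visit chosen by the sponsor, is tested at 0.05, and take the within-group time comparisons and the baseline group comparison out of its Bonferroni family. This needs no extra participants. The cost is that the time and baseline comparisons become descriptive. The sponsor must also say what status the other two primary measures and the remaining visits have.

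### Single-step Bonferroni is valid here, but Holm's step-down on the same families gives the same 5% guarantee and, under some conditions, more between-arm power

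*Protocol article*

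**What the plan says.** The Statistical analysis section of the protocol article sets out two routes and uses a one-step Bonferroni rule in both.

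- **ANOVA route** (normal, homogeneous data): "To protect against Type I error, Bonferroni’s correction will be used", followed by "Thus, each of the 10 planned comparisons will have to achieve" p = 0.005. The 10 comparisons are not listed.
- **Rank route, within arm:** Friedman, then Wilcoxon with Bonferroni "adjustment (*p* < 0.008) to compare evaluation time for each group".
- **Rank route, between arms:** Mann-Whitney with Bonferroni "adjustment (*p* < 0.012) will be used to compare the groups in each time evaluation". There are four evaluation times: baseline and 3, 30 and 90 days.

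No step-down procedure is mentioned. The only intervals described are ordinary 95% confidence intervals for pre-post change within each arm.

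The Sample size section derives 78 participants (39 per group) "using the independent t-test, 85% power, alpha 0.05, and 20% drop-out", without adjustment for multiple comparisons.

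**The concern.** A single-step rule holds every comparison in a family to the smallest threshold, even after other comparisons in that family have been clearly rejected. Holm's procedure orders the p-values and relaxes the threshold after each rejection. It controls familywise error at the same level under any dependence between the tests, and it can never reject fewer hypotheses.

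The main reason to prefer Bonferroni, simple simultaneous confidence intervals, does not apply because this plan uses none. What is at stake is power for the comparison of aerobic exercise with stretching. That power already falls short of the 85% used for sizing, because the tests are judged at thresholds well below 0.05.

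**Working it through.** **1. The plan's own thresholds**

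- ANOVA route: 0.05/10 = 0.005, exactly as stated.
- Wilcoxon: four visits give 4 × 3/2 = 6 pairs; 0.05/6 = 0.00833, stated as 0.008.
- Mann-Whitney: four visits; 0.05/4 = 0.0125, stated as 0.012.

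The last two are truncated, which is slightly conservative.

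**2. Holm on the same families**

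The k-th smallest of m p-values is compared with 0.05/(m − k + 1), stopping at the first failure.

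- Four tests: 0.0125, 0.0167, 0.025, 0.05.
- Ten tests: 0.005, 0.0056, 0.00625, 0.0071, and so on up to 0.05.

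The first step equals Bonferroni, so the smallest p-value gains nothing and the chance of at least one rejection in the family is identical. Only later steps gain, and only after an earlier rejection in the *same* family.

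**3. Inputs for the size of the gain**

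- Evaluable number: 39 × 0.8 = 31.2, taken as 31 per arm (31/0.8 = 38.75, rounded up to 39).
- Effect size: not given. Solving the two-sided t-test for 85% power at 0.05 with 31 per arm gives d = 0.774. This is an assumption, as is two-sidedness.
- Correlation between visits: 0.7 assumed (0.3 to 0.8 in the t-test range below).
- Gain from m-CIMT shared by both arms: about 0.6 SD assumed.
- Make-up of the 10 comparisons: assumed to be 6 time pairs and 4 group contrasts.

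**4. Power of one between-arm t-test at d = 0.774, 31 per arm**

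| Threshold | Power |
|---|---|
| 0.05 | 85% |
| 0.0125 | 68% |
| 0.05/7 = 0.0071 | 60.4% |
| 0.005 | 55.5% |

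The 0.05/7 row is the Holm threshold once three time contrasts out of ten have been rejected.

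**5. Simulated comparison (thousands of trials per scenario)**

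| Scenario | Bonferroni | Holm |
|---|---|---|
| Mann-Whitney, equal effect at three post visits: one given visit | 64% | 69% |
| Same, all three post visits | 45% | 56% |
| Same, at least one rejection | 82.5% | 82.5% |
| Assumed family of 10, equal effect: one given visit | 55% | 63% |
| Assumed family of 10, no exercise effect: any false group difference | 1.6% | 2.3% |

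With t-tests in place of Mann-Whitney tests and correlations of 0.3 to 0.8:

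- In the family of four with an equal effect at all post visits, per-visit power rises from 67–69% to 72–74%, and all-three power from 39–54% to 51–63%.
- In the family of four with an effect at day 3 only, the gain at day 3 is 0.0 to 0.2 percentage points.
- In the assumed family of ten, per-visit power rises from 55–57% to 58–64%, depending on how many time contrasts are rejected first.
- With no true effect, familywise error in the family of four is the same under both rules (3.6% to 4.6%).

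Holm rejected everything Bonferroni rejected in every simulated trial.

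**The case against.** The strongest reply is that Bonferroni is a standard, valid, prespecified choice whose thresholds agree with its counts, so nothing is wrong. That stands: this is a matter of efficiency. A reader might infer more, and three stronger readings fail.

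- **That Holm always gains power.** It does not. The gain in the Mann-Whitney family needs a rejection at another visit, and the documents do not say whether a priming effect would last from day 3 to day 90.
- **That easily rejected time contrasts release alpha to the arm contrasts in both routes.** In the rank route the Wilcoxon and Mann-Whitney tests are separate families, so nothing passes between them. In the ANOVA route it happens only if the unlisted 10 comparisons mix both kinds. The group-by-time interaction, which also carries the between-arm question, lies outside these figures.
- **That Bonferroni protects no better anywhere.** The 5% guarantee is the same. In a mixed family, though, Bonferroni does give a lower chance of a false group difference (about 1.6% against 2.3%), because Holm lets within-arm recovery loosen the between-arm threshold.

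It can also be said that the larger problem lies elsewhere: the trial was sized at 0.05 but its tests are judged at 0.005 or 0.012. That is right, and Holm closes only part of the gap.

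**Conclusion.** The point holds as a cheap efficiency gain, not as the correction of an error. For any make-up of the families, Holm keeps the 5% familywise guarantee and rejects at least as much as the stated rule.

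Under the assumptions shown, the gain for one between-arm comparison is about 5 percentage points in the Mann-Whitney family when the effect is equal at all post visits, and about zero when it is at one visit. In the ANOVA route it is about 8 points under the assumed mixed family with easily rejected time contrasts. Even then, power stays well below the planned 85%.

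That Holm never does worse is a property of the procedure. The sizes rest on the assumed effect size, correlation, shared gain, sidedness and family make-up. The sample size is also to be recalculated after the first five participants per group, so 31 per arm is itself provisional.

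**What to change.** Before unblinded analysis, replace Bonferroni in the Statistical analysis section by Holm's step-down procedure at familywise 5% within each stated family: the 10 planned comparisons, the 6 Wilcoxon tests in each arm, and the 4 Mann-Whitney tests. Drop the fixed thresholds 0.005, 0.008 and 0.012 and compare Holm-adjusted p-values with 0.05, which also removes the truncation.

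The text change is one or two sentences. In the ANOVA route the p-values of all 10 comparisons must be pooled into one list before adjustment. Simultaneous intervals that match Holm are less simple, but none are planned. In a mixed family the chance of a false group difference rises slightly and stays below 5%. The change does not replace reconciling the alpha used for sizing with the alpha used for testing.

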Considering a type of implicit learning, motor priming has been used in neurorehabilitation to facilitate motor learning [22, 26]. The priming theory presumes that when the brain is activated using an intervention delivered prior to the motor learning intervention, it will become more responsive to motor training due to increased neural activity. This “therapeutic window” may result from the modulation of long-term potentiation or long-term depression, such as mechanisms [22, 27, 28]. Movement-based priming, using repetitive or continuous, unilateral or bilateral movements, is an important method of priming the motor cortex in neurorehabilitation [22].

This protocol describes a single-blinded, randomized clinical trial designed to determine whether AE, as a form of movement-based priming, has an effect on the outcomes of m-CIMT, specifically the recovery of the skill of paretic upper limb in persons with chronic stroke. We hypothesize that AE will potentiate m-CIMT, resulting in improved manual dexterity in people in the chronic phase poststroke.

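### Neither quantity the plan names for the effect of the intervention on the parametric route is a signed aerobic-exercise-minus-stretching difference with a confidence interval

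*Protocol article*

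**What the plan says.** The Background states a directional, comparative hypothesis: "We hypothesize that AE will potentiate m-CIMT, resulting in improved manual dexterity". The Methods give m-CIMT to both groups; what differs is the 40-minute session before it (aerobic exercise or stretching).

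For variables that pass the normality and homogeneity checks, the Statistical analysis section of the protocol article plans a two-way repeated-measures ANOVA, whose stated aim is: "examine the effect of group-by-evaluation time interaction, group (AE + m-CIMT and Stretching + m-CIMT), and evaluation time (baseline, 3, 30 and 90 days". Follow-up visits are counted from the end of the intervention. The section then names two measures of effect in consecutive sentences:

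- Partial eta squared "will be used to determine the effect size of the intervention". The ANOVA has three terms, and the text does not say which one supplies the value.
- A within-group change: "The mean difference from pre- and post-interventions and the corresponding 95% confidence interval (95% CI) will be calculated for each group". The purpose given for this second measure is "in order to estimate the effect of the intervention".

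The section also sets a Bonferroni threshold: "each of the 10 planned comparisons will have to achieve" p = 0.005. It does not list the ten comparisons, and it states no between-group difference with an interval.

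**The concern.** The hypothesis asks whether adding AE makes dexterity better, by how much, and at which visit. Partial eta squared is a share of variance and cannot be negative. An AE benefit and an equal AE harm therefore give the same value, and for the interaction one number covers all four visits. It also carries no unit such as seconds, blocks or MAL points.

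The within-group changes do have sign and units, but each arm's change contains everything that happens to that arm, including ten days of m-CIMT. Calling that change the effect of the intervention invites a reader to credit AE with a gain the stretching arm also makes. If the trial reports only these two quantities, the size of aerobic priming has no direct estimate and no stated precision.

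**Working it through.** **The plan's own figure.** 0.05 / 10 = 0.005, so the stated threshold reproduces. The dispute is about what is estimated, not about this number.

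**Inputs from the article.** Two groups and four visits; N = 62 (Abstract) or 78 (Methods; "a sample size of 78 individuals (39 per group) is required for this study"). Both are carried because the article gives both. Interaction degrees of freedom are 3 and 3(N − 2): 3 and 180, or 3 and 228. Group degrees of freedom are 1 and N − 2.

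**Assumptions, not in the article.** Outcome SD 1, equal correlation ρ between visits, sphericity, and a common m-CIMT gain t at every post visit.

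**Step 1: partial eta squared when AE does nothing.** Its null mean is df1 / (df1 + df2).

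- Interaction: 3 / 183 = 0.0164 at N = 62, and 3 / 231 = 0.0130 at N = 78. The 95th percentiles are 0.042 and 0.034.
- Group: 1 / 61 = 0.0164 and 1 / 77 = 0.0130.

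The upward bias is real but small for these two terms.

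**Step 2: the time term when AE does nothing.** The squared deviations of (0, t, t, t) from their mean sum to 0.75t². The expected time sum of squares is N × 0.75t² + 3(1 − ρ), and the error is 3(N − 2)(1 − ρ). At N = 62:

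- t = 0.5, ρ = 0.5: (11.625 + 1.5) / (13.125 + 90) = 0.13.
- t = 0.8, ρ = 0.85: (29.76 + 0.45) / (30.21 + 27) = 0.53.

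These values reflect m-CIMT only.

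**Step 3: sign and visit.** A simulated 2 × 4 mixed ANOVA (5,000 runs per scenario, ρ = 0.7, t = 0.5) gave the following means. Changes are from baseline to day 3, in SD units.

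| Scenario | Interaction partial eta squared, N = 62 / 78 | Change, AE arm | Change, stretching arm | AE minus stretching |
|---|---|---|---|---|
| No AE effect | 0.0165 / 0.0127 | 0.50 | 0.50 | 0.00 |
| +0.5 SD at all post visits | 0.0659 / 0.0620 | 1.00 | 0.50 | +0.50 |
| −0.5 SD at all post visits | 0.0654 / 0.0623 | 0.00 | 0.50 | −0.50 |
| +0.5 SD at day 3 only | 0.0649 / 0.0615 | 1.00 | 0.50 | +0.50 |

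The algebra agrees. At N = 62 the expected interaction sum of squares is 62 × 0.75 × 0.25 / 4 + 0.9 = 3.806 and the error is 180 × 0.3 = 54, so the ratio is 3.806 / 57.806 = 0.066. The effect enters squared, so its sign is lost. A gain at one post visit and a gain at all three have the same sum of squared deviations, so the interaction value cannot tell them apart.

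**Step 4: what the within-group intervals show.** With ρ = 0.7 the SD of change is √(2 × 0.3) = 0.775. With 31 per arm its standard error is 0.775 / √31 = 0.139, and the 95% half-width is about 1.96 × 0.139 = 0.27. With no AE effect, each arm is expected to report about 0.50 (0.23 to 0.77), clear of zero. The difference between arms is 0.00 with standard error 0.139 × √2 = 0.197, so about −0.39 to +0.39. Only this last interval addresses the hypothesis, and the section does not name it.

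**The case against.** The strongest reply is that partial eta squared is not the plan's only measure of effect. The next sentence plans signed changes in native units with intervals, so direction can be read by setting the two arms side by side; in the table above, harm shows as 0.00 against 0.50. That stands. A reader might infer that the plan cannot tell benefit from harm, or that its results could not be set against a meaningful change on any scale. The document does not support that for the plan as a whole, only for partial eta squared taken alone. What remains is that two within-arm intervals do not give the interval for their difference.

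A reader might also infer that partial eta squared systematically flatters AE. For the interaction and group terms the null mean is only about 0.013 to 0.016. The large values need the time term to be the one reported, and the article does not say so. It lists the interaction first, which is the term that fits the hypothesis.

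It is fair, too, that partial eta squared is a routine companion to repeated-measures ANOVA and drives no test, threshold or sample size here. The ten comparisons may well include between-group ones: four visits give six pairs within time and four group contrasts, 6 + 4 = 10. But the text gives these a significance threshold only, not an estimate with an interval.

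Finally, the article names no effect measure for the rank route. A condensed article may leave that to the full plan, so it is not counted as a fault.

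**Conclusion.** The point holds for the parametric route. The article itself fixes two quantities as the effect of the intervention, so this is a stated choice and not a detail left to a fuller plan. One quantity is unsigned, pooled over visits and not tied to a term. The other is within arm and contains the m-CIMT gain common to both groups. Neither is AE minus stretching with an interval.

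The size depends on use. If partial eta squared comes from the interaction, the null bias is minor (0.016 at N = 62 and 0.013 at N = 78, assuming sphericity), and the loss is of sign, visit and unit. If it comes from the time term, a value of about 0.13 to 0.53 could be attached to AE when AE adds nothing. That range rests on an assumed gain of 0.5 to 0.8 SD and correlation of 0.5 to 0.85 at N = 62; none of the article's figures confirms it. The hypothesis tests are unaffected. The change should be made before analysis because it determines whether the reported magnitude answers the trial's question.

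**What to change.** In the Statistical analysis section, define the effect of the intervention as the difference between groups (AE + m-CIMT minus Stretching + m-CIMT) in change from baseline at 3, 30 and 90 days, in the outcome's own units with a 95% confidence interval. Hedges' g may be added if a standardised value is wanted. For outcomes that take the rank route, give the Hodges-Lehmann shift between groups with a 95% confidence interval, so that both routes report a comparable quantity.

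Keep the within-group changes as descriptive. If partial eta squared is kept, label it descriptive and tie it to the group-by-time interaction.

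The cost is a sentence or two and a little extra reporting. The data, tests and sample size stay as they are, and standard software gives every quantity.
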